### Program Implementation Plan

For convenience, the three secondary schools included in our concept mapping study were asked to pilot the intervention. Two more secondary schools, each characterized by similar features as the already recruited ones, that is, in terms of regions, educational levels, and grades, will be searched by sending random invitation letters. Similar random invitation letters will also be sent to recruit secondary schools in the main study.

The school year in Germany starts in fall and ends in summer, whereby the first term ends in spring. In previous research from Norway, seasonal differences in cycling to school were observed between fall (52%), winter (3%), and spring (51%) (30) as well as between winter (12%) and summer (22%) (31). Also in Germany, cycling to school decreases in winter (32). Therefore, the implementation of the intervention should start in fall and end in spring (i.e., during the first term of the school year). According to the preparatory and practical phases, individual components will be implemented one after another at the participating secondary schools over a period of 5 months (see Table 3). As implemented components will prepare students for the possibly more difficult (weather) conditions in winter, we do not expect a negative seasonal influence on the effectiveness of the intervention. For example, information about appropriate clothes will be provided during the joint parents', teachers', and students' evening. Furthermore, parents and teachers will be reminded of serving as role models so that the 12- to 15-year-olds learn how to establish a cycling routine regardless of (weather) conditions in winter. Students will feel safer and more confident in dealing with difficult road conditions after participating in the cycle training, which will improve their basic cycling skills and practice them on-road (e.g., handling obstacles and appropriate driving style). The bicycle train will increase the motivation and safety of students through positive experiences when accompanied by and interacting socially with peers instead of cycling to school alone in the darkness. Furthermore, the bicycle train will establish a new social norm (i.e., cycling to school as an activity throughout the whole year, including winter and not only in summer). The intervention will follow a whole-of-school approach as we designed components that will take place before, during (i.e., in art and physical education (PE) lesson), and after school. At each participating secondary school, a person of contact will be defined who will act as a coordinator for implementing the intervention. Furthermore, the person of contact will interact with the responsible implementers at their school (i.e., PE and art teacher) and a researcher as well as the project manager at the Technical University of Munich (TUM) who can be called or e-mailed any time in case of occurring questions or problems. The researcher from TUM will be in touch with the person of contact to organize data collections and the implementation of components, which will be led by the researcher and student assistants from TUM. As our aim was to draft a sustainable intervention, we will provide secondary schools with all materials needed for the replication of the intervention and initiate several collaborations with government facilities (i.e., police) and nongovernmental organizations (e.g., ADAC) free of charge that can be continued after we will have left schools.

**Table 3 T3:** Program implementation plan.

**Phases**	**Weeks**	**Components**	**Locations**	**Time frame**	**Implementers**	**Tasks to be prepared**
Preparation	1	Joint parents', teachers', and students' evening	School assembly hall and online	After regular school hours (1 × ca. 150 min)	Person of contact at school	1. Finding a possible date and communication to the researcher at TUM2. Handing invitations out to students for their parents and to teachers3. Preparing assembly hall (e.g., chairs, media)
					Researcher and student assistant from TUM	1. Drafting an invitation letter for parents and teachers2. Preparing lecture/materials (i.e., booklet, video)3. Preparing assembly hall (e.g., chairs, media)
	2	Bicycle inspection in the presence of parents and provision of required bicycle-related equipment	School's playground	After regular school hours (1 × ca. 180 min)	Person of contact at school	1. Finding a possible date and communication to the researcher at TUM2. Handing invitations out to students for their parents3. Helping to prepare the event4. Handing bicycle equipment out to students
					Researcher and student assistant from TUM	1. Contacting the ADFC, asking for a collaboration, and what is needed to perform the event2. Drafting an invitation letter for parents3. Preparing the event (e.g., materials)4. Organizing missing bicycle equipment
					ADFC	Preparing and performing bicycle inspection
	2	Personalization of bicycle-related equipment	Classroom	During regular art lesson (1 × 45 min)	Art teacher	Supervision
	3–7	Cycle training sessions (incl. improvement of basic cycling skills, information about traffic rules, practicing social behavior)	Off-/on-road	Once per week during regular PE lesson (90 min): Off-road (3x), knowledge transfer (1x), on-road (1x)	PE teacher	Realization of lesson plans
					Researcher from TUM	1. Drafting detailed lesson plans2. Preparing materials (i.e., obstacles, booklet)3. Handing lesson plans and materials out to teachers
	8	Final exam of basic cycling skills in the presence of parents (incl. provision of a certificate)	School's playground	After regular school hours (1x ca. 180 min)	Person of contact at school	1. Finding a possible date and communication to the researcher at TUM2. Handing invitations out to students for their parents3. Helping to prepare the event
					Researcher and student assistant from TUM	1. Contacting the ADAC, asking for a collaboration, and what is needed to perform the event2. Drafting an invitation letter for parents3. Preparing the event (e.g., drafting certificates for each participating student)
					ADAC	Preparing and performing final exam
Practice	9–20	Voluntary bicycle train to cycle to school among peers with an arranged route and stops (incl. events)	On the way to/from school	5x to and 5x from school per week (i.e., before and after school) with 1 event per month	Researcher from TUM	Contacting the responsible police station, asking for a collaboration, and what is needed to perform the event
					Police	Supporting the cycling-to-school-events (e.g., kick-off event)

*ADAC, German Automobile Club; ADFC, German Cyclist's Club; ca., circa; incl., inclusive; PE, physical education; TUM, Technical University of Munich*.

### Evaluation Plan

To report the findings of our planned evaluation, the “CONSORT 2010 statement: extension to cluster randomized trials” (33) will be followed.

#### Study Design

The main study is planned as a two-arm (i.e., intervention and control group (IG; CG)) three-level cluster (i.e., students in classrooms in schools) RCT (see Figure 4), whereby a simple randomization technique (i.e., flipping a coin) on school-level was chosen. For convenience, the pilot study will follow a quasi-experimental study design as a non-RCT. Directly before and after the implementation of the intervention, a pre- and post-measurement will take place as part of the effect evaluation. Furthermore, the process evaluation will take place during and after the implementation of the intervention. Based on the intraclass correlation coefficient (ICC) of 0.2 calculated for the variance of days per week students cycled to school between the three secondary schools in our concept mapping study (17), we assigned more than one secondary school to the IG and CG. No treatment will be delivered to the CG. In the main study, approximately 255 students belonging to five schools with two classes in grade(s) 7 and/or 8 will be in the IG and CG, respectively. However, approximately 150 students belonging to three schools will be in the IG and 100 students belonging to two schools in the CG when piloting the intervention.

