In step one of the IM protocol, the logic model of the problem was created (see Figure 2). Here, the needs of students to cycle to school daily were assessed using a concept mapping study (17). In total, 136 students aged 12–15 years attending grade 7 or 8 at three different secondary schools of different educational levels located in different sub(urban) regions in Southern Germany participated in the study. For a more comprehensive understanding of the behavior of the students, concept mapping was also performed among students' parents (*n* = 58) and teachers (*n* = 29) of both genders female and male, whereby the low retention rate of fathers did not permit a separate gender analysis. As needs to cycle to school daily, a “bicycle and related equipment,” the “way to school,” and “personal factors” were mentioned by all three analyzed samples of students, mothers, and teachers. Additionally, students mentioned “cycle training,” mothers mentioned the “role of the school,” and the teachers mentioned “storage and changing room,” “financial aspects,” as well as “information and services.” Furthermore, “social behavior in road traffic” was mentioned by girls only, “role of parents” by mothers and female teachers, and “sense of safety” by female teachers. As none of these mentioned needs stood out as particularly (un)important and/or (un)feasible, we treated all of them as equally relevant. In this study, almost all students owned a bicycle (girls: 87.8%, boys: 100%) and all were able to cycle (5). When examining the habits of the students in cycling to school, we found that approximately two-thirds of students stated to sometimes cycle to school (girls: 44.4%, boys: 72.9%), of whom approximately one-third cycled to school daily (girls: 31.6%, boys: 37.3%). On average, students generally cycled to school on 2.3 ± 2.0 days per week (girls: 1.6 ± 2.0, boys: 2.7 ± 2.0). Moreover, the following correlates were identified to be negatively associated with cycling to school habits of students: (a) being a girl, (b) increasing age (mainly in girls), (c) attending an intermediate educational level in combination with a suburban region of the school, (d) attending a school located in a small town (mainly in girls) or a medium-sized town, (e) living further away from school, and (f) having parents not using a bicycle to commute to work.

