#### Sample Size Determination

The optimal sample size for our chosen study design in the main study was calculated based on a formula by Rutterford et al. (34). This formula considers the confidence level (97.5%), power (80%), variance of days per week in cycling to school at the individual level [4.1 days (5)], our estimated clinically important difference in treatment means of days per week in cycling to school at the individual level (1.75 days), number of students per secondary school (based on the mean value in our concept mapping study: 51 students), and ICC of days per week students cycled to school at school level [0.2 days (17)]. According to this formula, the required number of students per intervention condition is 231. For the planned pilot study in the first instance, 10% of the main study's calculated sample size is recommended (35, 36) (i.e., 23 students per arm).

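### Coin-flip allocation of ten schools does not deliver the planned five schools per arm: 5:5 arises in 24.6% of draws, and average power on the plan's own formula falls from 83.7% to 78.9%

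*Protocol article*

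**What the plan says.** The Study Design section of the protocol makes three statements about the main study that have to be read together.

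- Allocation is by school: "whereby a simple randomization technique (i.e., flipping a coin) on school-level was chosen".
- The arms are fixed in size: "approximately 255 students belonging to five schools with two classes in grade(s) 7 and/or 8 will be in the IG and CG, respectively".
- Because of the between-school ICC of 0.2, single-school arms are to be avoided: "we assigned more than one secondary school to the IG and CG".

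The Sample Size Determination section requires 231 students per arm. At 51 students per school this is 231/51 = 4.53, hence five schools and 5 × 51 = 255 students per arm.

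The Logic Model of the Problem section lists correlates of less cycling to school. Two of them are school attributes: "attending an intermediate educational level in combination with a suburban region of the school", and the school's location in a small or medium-sized town. The protocol does not say that allocation takes account of either.

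**The concern.** Simple randomization means that each school is allocated independently of the others, so the number of schools per arm is left to chance. A fixed five per arm needs a restriction. The two statements stand in the same section and cannot both be followed as written.

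With hundreds of individually randomized participants the discrepancy would be trivial. Here only ten units are allocated, and a marked imbalance in the number of schools is a common result. At stake are the precision of the treatment comparison and, in rare draws, whether the trial can be analysed as designed. The allocation cannot be repaired once schools have been assigned.

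**Working it through.** **Inputs (Sample Size Determination).** Variance of days per week 4.1; difference 1.75 days; 51 students per school; school-level ICC 0.2; power 80%; confidence level 97.5%. The last is used as z = 1.960, because that value reproduces the plan's figure.

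**Step 1: reproduce the plan's figure.** The formula is n per arm = 2 × variance × (z for confidence + z for power)² / difference² × [1 + (m − 1) × ICC].

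- Without clustering: 2 × 4.1 × (1.960 + 0.842)² / 1.75² = 21.02.
- Design effect: 1 + 50 × 0.2 = 11.
- Product: 21.02 × 11 = 231.2, which matches the stated 231.

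**Step 2: distribution of the split.** Ten independent fair flips give a Binomial(10, 0.5) count of intervention schools, with 2¹⁰ = 1024 equally likely outcomes.

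- 5:5: 252/1024 = 24.6%
- 6:4 in either direction: 420/1024 = 41.0%
- 7:3 or worse: 352/1024 = 34.4%
- 8:2 or worse: 112/1024 = 10.9%
- An arm with no school or one school: 22/1024 = 2.1%

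**Step 3: power by split, with the plan's normal approximation.** The variance of one school mean is 4.1 × 11 / 51 = 0.884. For k1 and k2 schools, SE = √[0.884 × (1/k1 + 1/k2)], and power = Φ(1.75/SE − 1.960).

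| Split | Students | SE | Power | Probability |
|---|---|---|---|---|
| 5:5 | 255 / 255 | 0.595 | 83.7% | 24.6% |
| 6:4 | 306 / 204 | 0.607 | 82.2% | 41.0% |
| 7:3 | 357 / 153 | 0.649 | 76.9% | 23.4% |
| 8:2 | 408 / 102 | 0.743 | 65.3% | 8.8% |
| 9:1 | 459 / 51 | 0.991 | 42.3% | 2.0% |
| 10:0 | 510 / 0 | none | 0% | 0.2% |

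**Step 4: average over the coin.** Weighting the powers by their probabilities gives 78.9%. The average loss against a fixed 5:5 is 83.7 − 78.9 = 4.8 points. Power is below 80% in the draws at 7:3 or worse, that is in 34.4%.

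**Step 5: does the loss depend on the approximation?** A t test on ten school means (8 degrees of freedom) gives 73.2% at 5:5 and 68.2% averaged over the coin, a loss of 5.0 points. The levels are lower, but the cost of the coin is almost the same.

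**The case against.** Simple randomization is a valid procedure, 5:5 is the single most likely split, and most draws do little harm. A 6:4 split costs 1.5 points of power and stays above 80% on the plan's formula. Together 5:5 and 6:4 cover 65.6% of draws. All of this stands, and it limits the size of the point.

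It might also be said that the coin could be flipped within matched pairs, or until one arm holds five schools. Either would give 5:5, but neither is simple randomization and the protocol describes neither. The article is a condensed document, but it names the method and the arm sizes outright, so the conflict lies in what it states, not in what it omits.

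Four stronger readings are tempting and should not be drawn.

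- **An arm below 231 students means failure.** Any split other than 5:5 leaves one arm with at most 204 students. However, 231 is derived for equal arms, and at 6:4 the larger arm nearly makes up for the smaller one.
- **An unequal split loses degrees of freedom.** It does not. With ten schools there are 8 for every split in which both arms are filled. The loss comes through the standard error alone.
- **Chance imbalance confounds the treatment effect.** After random allocation it adds variance and can distort a single trial's result, but it does not bias the comparison. The plan also has a pre-measurement, a repeated-measures model, and school educational level and region among the moderators. The protocol gives no effect sizes for these correlates and warns in its Introduction that such associations may vary with context.
- **The coin brings power down to about 70%.** The fall from 83.7% to 73.2% at 5:5 comes from having few clusters. It is a separate matter that restricted allocation does not cure.

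**Conclusion.** The point holds as an inconsistency with a moderate cost. The stated allocation rule yields the stated design in about one draw in four. It costs about 5 points of power on average, puts power below the plan's 80% in about a third of draws, and in 2.1% of draws breaks the plan's intention of more than one school per arm.

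The figures assume ten schools, independent fair flips, 51 students in every school, and the plan's own variance, difference and ICC. They describe a comparison of post-measurement means, as the plan's formula does, so adjustment for the pre-measurement would change the power levels. The split probabilities depend only on the ten flips. The pilot is non-randomized, with three schools against two, and is not affected.

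**What to change.** In Study Design, replace the coin flip with a single restricted random draw that assigns exactly five of the ten schools to each arm, made once all ten schools are recruited. This brings the allocation rule into line with the five schools per arm and with the sample size calculation, and it keeps the 83.7% that the plan's formula gives at 5:5.

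Where feasible, pair-match the schools or constrain the draw on educational level and town type to limit chance imbalance. Full stratification is not advisable: two educational levels by three town types make six cells for ten schools. Extra school-level terms in the model are not needed for this fix and would use up scarce degrees of freedom.

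The cost is a sentence or two in the protocol, a short documented draw, and waiting for the tenth school before any school learns its arm. As the main study follows a pilot, there is time to make the change.

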**Figure 4 F4:**
[figure not shown]
Study design of the planned cycling to school intervention. *N*, sample size.

#### Sample Size Determination

The optimal sample size for our chosen study design in the main study was calculated based on a formula by Rutterford et al. (34). This formula considers the confidence level (97.5%), power (80%), variance of days per week in cycling to school at the individual level [4.1 days (5)], our estimated clinically important difference in treatment means of days per week in cycling to school at the individual level (1.75 days), number of students per secondary school (based on the mean value in our concept mapping study: 51 students), and ICC of days per week students cycled to school at school level [0.2 days (17)]. According to this formula, the required number of students per intervention condition is 231. For the planned pilot study in the first instance, 10% of the main study's calculated sample size is recommended (35, 36) (i.e., 23 students per arm).

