The decision to publish the detailed process of how our intervention was planned can be seen as a major strength as we demonstrate transparency of our structured procedure for other intervention planners. To the best of our knowledge, this is the first time that IM was used to plan an intervention aimed at the promotion of cycling to school. Our planned intervention has also several strengths: We chose the school setting for our intervention because it is regarded as ideal (50–53). According to the “Standing Conference of the Ministers of Education and Cultural Affairs” in Germany (54), the task to provide mobility and traffic education is assigned to schools, which we support with our planned intervention. Our intervention will contribute to closing the currently existing research gap by focusing on secondary schools where ACTS, especially cycling to school, is currently the least implemented activity (10) and generally, in an early development stage (9) with a lack of evidence for effectiveness in the majority of existing school-based interventions (11). We decided to focus on the promotion of cycling to school in winter (32) among the high-risk ACTS group of 12- to 15-year-olds (55) attending grade 7 or 8 (11) to expand the current state of research. As recommended, we chose a whole-of-school approach (56), a multi-level approach (21, 57), and a combination of objective as well as subjective measuring instruments to accurately assess the PA level during cycling (58). To prevent negative experiences on-road (e.g., accidents), we will first provide some theoretical and practical components off-road. Instead of choosing a top-down approach, we partly chose a participative approach to consider the opinion of the target group (i.e., students) and relevant stakeholders (i.e., parents and teachers), to address the local context appropriately, and to ensure the feasibility of the implementation of the intervention. The success of this approach will be controlled in the process evaluation. Furthermore, we will initiate collaborations (e.g., with the ADAC and police) free of charge and provide all necessary materials so that schools could continue the work beyond the duration of the intervention, which will ensure sustainability. Finally, we determined the appropriate sample size for an adequately powered effect evaluation, will control for potential mediators and moderators in our analysis (57) and will pilot the intervention. The purpose of piloting is to pre-test the effectiveness, acceptance, and feasibility of the intervention, as it will later be performed in the main study, in accordance with the planned organizational procedure and chosen measuring instruments for data collection described in this study protocol but by using a smaller sample size and a weaker, that is, quasi-experimental, study design.

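### With five schools per arm, the plan's own inputs give about 73% power for 1.75 days, because the 231 comes from a large-sample formula

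*Protocol article*

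**What the plan says.** Sample Size Determination in the protocol article names a published formula and lists its inputs: a 97.5% confidence level, 80% power, an outcome variance of 4.1, a difference of 1.75 days per week, 51 students per school and a school-level ICC of 0.2. It concludes: "According to this formula, the required number of students per intervention condition is 231".

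Study Design describes a two-arm "three-level cluster (i.e., students in classrooms in schools) RCT", randomised by coin flip at school level. Each arm is to have five schools with two classes each, about 255 students. The same section says that the ICC of 0.2 was calculated from the variance between the three schools of the concept mapping study.

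Statistical Analysis plans a model with four levels: repeated measurements, students, classes and schools. The Discussion counts among the strengths that "we determined the appropriate sample size for an adequately powered effect evaluation".

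**The concern.** The requirement is expressed in students, and 255 planned against 231 required looks like a comfortable reserve. The unit of randomisation is the school, however, and there are ten of them. A formula with normal quantiles is reliable when there are many clusters. With ten schools the between-school variance has to be estimated from very few units, and the critical value is about 2.31 instead of 1.96. The apparent reserve could then be a shortfall, and the claim of adequate power would rest on the formula and not on the design. If so, a true effect of 1.75 days would be missed about 27% of the time, where the plan accepts 20%.

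**Working it through.** **Inputs.** From Sample Size Determination: variance 4.1, difference 1.75, m = 51 students per school, ICC 0.2, power 80%, confidence level 97.5%. From Study Design: k = 5 schools per arm, randomised by school. Sidedness is not stated. The 97.5% is read as the quantile 1.96 (two-sided 5%), because that reading reproduces the plan's figure; a two-sided 2.5% level would give 280.

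**Step 1: reproduce the plan's figure.**

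- Students per arm without clustering: 2 × 4.1 × (1.960 + 0.842)² / 1.75² = 21.016
- Design effect: 1 + (51 − 1) × 0.2 = 11
- Students per arm: 21.016 × 11 = 231.17, matching the stated 231. This is 231.17 / 51 = 4.53 schools.

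The text does not name normal quantiles. They are inferred from this match.

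**Step 2: standard error for the planned design.**

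- Variance of one school mean: 4.1 × 11 / 51 = 0.884. Of this, 0.2 × 4.1 = 0.820 lies between schools and 0.8 × 4.1 / 51 = 0.064 comes from students within a school.
- Standard error of the difference: √(2 × 0.884 / 5) = 0.595 days
- Noncentrality: 1.75 / 0.595 = 2.94

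About 93% of the variance of a school mean (0.820 / 0.884) is between schools, so enrolling more students in the same schools adds almost nothing.

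**Step 3: power.**

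| Basis (5 schools × 51 students per arm) | Critical value | Power for 1.75 days |
|---|---|---|
| Normal approximation | 1.96 | 83.7% |
| t with 2 × 5 − 2 = 8 df | 2.31 | 73.2% |

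A simulation of school means under the same assumptions gave 73.4%.

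**Step 4: detectable difference.** For 80% power with 8 df the noncentrality must be 3.20, so the difference is 3.20 × 0.595 = 1.90 days.

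**Step 5: what baseline adjustment would have to deliver.** To restore 80% for 1.75 days, the variance of school means must shrink to (2.942 / 3.201)² = 0.845 of its value if 8 df are kept. If one df is spent on a school-level covariate (7 df, noncentrality 3.27), it must shrink to (2.942 / 3.270)² = 0.810. Adjustment must therefore remove about 15% to 19% of that variance.

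**Step 6: number of schools.** Six schools per arm (306 students) give a noncentrality of 3.22 with 10 df, and 82.7% power without baseline credit.

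**The case against.** **Baseline adjustment.** The strongest objection is that 73% is the power of a post-only comparison of school means, while the plan has a pre-measurement and models repeated measurements. If covariate adjustment acted equally at student and school level, an assumed pre-post correlation of about 0.4 would restore 80% with 8 df, and 0.5 would give 84%. This stands as a possibility. It does not support the printed figure, because the calculation takes no such credit and the article states no correlation.

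**Uncertain inputs.** The ICC comes from three schools. With the same t test, an ICC of 0.15 gives 83% power and 0.25 gives 64%. The 73% is therefore no precise forecast. It is what the plan's own inputs imply, which is the basis on which the plan claims 80%.

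**Correct arithmetic.** The article says that 231 follows from its formula, and it does. That is conceded: the fault is in applying a large-sample formula to ten schools.

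**Class clustering.** A reader might infer a further loss, since design and analysis declare a class level and the listed inputs contain no class ICC. If assumed class shares of 0.02, 0.05 or 0.10 are added on top of the 0.2, power falls to 71%, 69% or 65%. The document does not support restating the power on that basis. It gives no class ICC, and it describes the 0.2 as calculated from variance between schools, with no class term mentioned. With two classes per school, such an estimate may already contain about half the class variance. Taking a school share of 0.2 − c/2 and a class share of c, power stays at about 73% for the same three values. A loss from classes is a possible direction, with no size that can be derived from the article.

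**Conclusion.** The point holds, as a fault in the choice of formula. On the plan's own inputs, five schools of 51 students per arm give about 73% power for 1.75 days, some 7 points below the stated 80%, or a detectable difference of about 1.90 days at 80%. The Discussion's claim of adequate power is not supported as written.

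This rests on a two-sided 5% test, exactly five equal schools per arm, an ICC of 0.2, no loss of schools or students, and no credit for the pre-measurement. It needs no class-level ICC. It would be wrong to conclude that the trial cannot reach 80%: with enough baseline correlation it could, but the plan neither makes that assumption nor gives a figure for it.

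**What to change.** In Sample Size Determination, restate the planned power as about 73% for 1.75 days, or the detectable difference at 80% power as about 1.90 days, computed with t quantiles on 8 degrees of freedom. Give the requirement in schools as well as students. Bring the statement on power in the Discussion into line.

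If 80% for 1.75 days is to be kept by crediting the pre-measurement, state that assumption: adjustment must remove about 15–19% of the variance of school means. If 80% is wanted without that credit, six schools per arm would give 82.7% on the stated inputs.

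Restating the figure costs the rewording of one paragraph and one sentence, and a less favourable number. It needs no extra schools. The main study follows the pilot, so the change can still be made before schools are recruited for it.
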